#### Sample estimation

*Sample size for nurse midwives*. The sample size for the intervention and control group of nurse midwives will be obtained by using the formula for comparing two independent samples (intervention group vs control group), guided by the study by Joho [40]. In her study, which is conducted in 39 primary health facilities in Dodoma, she found that the knowledge proportion of nurses on the timing of administration of uterotonic before and after the educational intervention was 44.8% and 63.4%, respectively [40,43].

$$n=2\{Z_{\alpha }\sqrt{[\pi_{0}}(1‐\pi_{0})]+Z_{\beta }\sqrt{[\pi_{1}}(1‐\pi_{1})]\}/{\left(\pi_{1‐}\pi_{0}\right)}^{2}$$

n = Minimum sample size

Zα = Standard normal deviation of 1.96 at 95% confidence interval (CI).

Zβ = Standard normal deviation 0.80 with the power demonstrating statistically significant difference before (baseline) and after intervention between two groups at 80%.

p0 = Proportion of an intervention group at baseline = 44.8% (0.448)

p1 = Proportion after the intervention = 63.4% (0.634)

With a 5% attrition rate:

$$n=2\{1.96\sqrt{\left[0.634(1-0.634)\right]}+0.8\sqrt{\left[0.448(1-0.448)]\right\}}/{\left(0.634‐0.448\right)}^{2})$$

n = 78

So, the minimum sample size will be 78 plus a 5% attrition rate = 82

The ratio of the intervention group to the control group will be 1:2. Therefore, the sample size for the control group will be 164.

Thus, the total sample size in this study will be 246 nurse midwives.

*Sample size for post-CS mothers*. The sample size for the intervention and control group of post-CS mothers will be obtained by using the following formula;

The formula for comparing two independent samples (intervention group vs. control group), and using the proportion of SSI for pre-intervention was 16% and 4.9% for post-intervention [44]. A prospective observational cohort study involving active in-patient and post-discharge surveillance cohort study was done in DRRH at Obstetrics and Gynaecology Department where [43];

$$n=2\{Z_{\alpha }\sqrt{[\pi_{0}}(1‐\pi_{0})]+Z_{\beta }\sqrt{[\pi_{1}}(1‐\pi_{1})]\}/{\left(\pi_{1}‐\pi_{0}\right)}^{2}$$

n = Minimum sample size

Zα = Standard normal deviation of 1.96 at 95% confidence interval (CI).

Zβ = Standard normal deviation 0.8 with the power demonstrating statistically significant difference before (baseline) and after intervention between two groups at 80%.

p0 = Proportion of an intervention group at baseline = 16% (0.16)

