### Analysis of SSI

Binary logistic regression analysis will be used to assess factors associated with SSI.

The general logistic regression model is given as:

$$\log it[\pi (x)]=\log(\frac{\pi (x)}{1-\pi (x)})=\beta_{0}+\beta_{1}x_{1}+\ldots \ldots +\beta_{p}x_{p}$$

Where *π*(*x*) is the SSI status, *x*_*i*_’*s* is set of independent variables and *β*_*i*_’*s* is their respective parameters.

The power of the study will be set at 80% (0.8) while a confidence interval of 95% with a margin of error of 5% (0.05) was used as a statistical measure of significance (< 0.05 was regarded as significant while > 0.05 not significant).

The effect of intervention between groups will be assessed using difference in difference (DID) analysis.

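### The 80% power stated for nurse-midwife knowledge comes from a two-independent-proportions formula, not from the planned pre/post controlled contrast, which reaches 80% only if the pre-post correlation is about 0.5 or more

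*Protocol article*

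**What the plan says.** Protocol article, *Sample estimation*: the nurse-midwife number is obtained from the "formula for comparing two independent samples (intervention group vs control group), guided by the study" of an earlier educational intervention. The inputs are 44.8% with adequate knowledge before training and 63.4% after. The power term is given as "Zβ = Standard normal deviation 0.80 with the power demonstrating statistically significant difference before (baseline) and after intervention between two groups at 80" per cent. The result is 78, raised to 82 for 5% attrition, with 164 controls at a 1:2 ratio and 246 in total.

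The Phase 4 *Study design* is quasi-experimental, with pre- and post-tests and a non-equivalent control group. *Analysis of knowledge of home care after CS* plans a generalised estimating equation for the binary knowledge outcome, because each participant is measured more than once. *Analysis of SSI* repeats the 80% figure and ends: "The effect of intervention between groups will be assessed using difference in difference (DID) analysis".

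**The concern.** The power statement describes a before/after difference between two groups, which is a contrast of four proportions. The formula contains only two. The variance of the four-proportion contrast includes the baseline terms of both groups and is reduced by the within-person covariance. Neither enters the calculation, so the 80% does not describe the contrast that the design and the GEE are there to estimate.

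Nurse knowledge is a stated effectiveness objective. The two hospitals were chosen, not randomised, so the baseline-adjusted contrast matters more than a post-only one. If its power is well below 80%, a non-significant result could be misread as evidence that the training does not work.

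**Working it through.** **Inputs from *Sample estimation*:** p0 = 0.448, p1 = 0.634, z = 1.96, Z-beta entered as 0.80, 78 and 82 in the intervention group, 1:2 ratio. Evaluable controls are 2 × 78 = 156; enrolled controls are 164.

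**Assumptions, not in the document:** controls start at 44.8% and stay there; the pre-post correlation r is the same in both arms; test two-sided at 0.05.

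**1. The plan's own figure.** p0(1−p0) = 0.2473 and p1(1−p1) = 0.2320, with square roots 0.4973 and 0.4817. The printed substitution gives

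2 × (1.96 × 0.4817 + 0.80 × 0.4973) / 0.186² = 2 × 1.3420 / 0.034596 = 77.6, so 78.

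With p0 and p1 in the order of the symbolic formula it gives 78.6. The plan's 78 therefore reproduces, but only without squaring the braces. Squaring them gives 2 × 1.3420² / 0.034596 = 104. The normal deviate for 80% power is 0.84; 0.80 is the power itself. With the square and 0.84 the substituted form gives 107. The standard two-proportion calculation needs 112 per arm at 1:1, or about 84 in the smaller arm at 1:2.

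**2. Post-only comparison.** At 78:156 the unpooled standard error is √(0.2320/78 + 0.2473/156) = 0.0675, and power is Φ(0.186/0.0675 − 1.96) = 79%. With a pooled null variance it is 77%. At 82:164 the pooled figure is 79%.

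**3. Group-by-time contrast, risk-difference scale.**

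Var = [0.2320 + 0.2473 − 2r × 0.2395]/n1 + 2 × 0.2473 × (1 − r)/n0

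Power = Φ(0.186/SE − 1.96)

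| r | SE at 78:156 | Power at 78:156 | Power at 82:164 |
|---|---|---|---|
| 0 | 0.0965 | 49% | 51% |
| 0.2 | 0.0863 | 58% | 60% |
| 0.4 | 0.0748 | 70% | 72% |
| 0.5 | 0.0683 | 78% | 80% (79.8%) |
| 0.6 | 0.0611 | 86% | 88% |

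Power reaches 80% at r = 0.527 for 78:156 and at r = 0.503 for 82:164.

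**4. Same contrast on the logit scale, as a GEE group-by-time term.** At 78:156 power is 57%, 69%, 77% and 85% for r = 0.2, 0.4, 0.5 and 0.6. At 82:164 it is 59%, 71%, 79% and 87%. The scale makes little difference.

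**5. Attainable correlation.** With margins of 44.8% and 63.4%, the largest possible r between the two binary scores is (0.448 − 0.448 × 0.634)/0.2395 = 0.68. That maximum requires every nurse adequate before training to remain adequate after it.

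**6. Mothers, SSI.** A two-group comparison at 152:304 with 16% v 4.9% has about 96% power.

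**The case against.** Four points can be made against this, and each limits it.

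- **Where the DID sentence stands.** A reader might infer that the protocol specifies difference-in-differences as the test of nurse knowledge. It does not: the sentence is under SSI, and GEE is named for knowledge. The substance survives, because SSI has no baseline in the same mothers and a GEE group-by-time term has nearly the same power (steps 3 and 4). The article does not spell out that term, though it is the natural reading of a GEE in a pre/post controlled design.
- **The correlation is assumed.** A reader might take 49% as the trial's power. That needs r = 0, meaning a nurse's pre-test says nothing about the same nurse's post-test, which is extreme when intervention nurses are post-tested on the day of training. If no trained nurse loses adequacy, r in that arm is 0.68, and power at 78:156 is 74%, 79%, 82% and 88% for control-arm r of 0, 0.2, 0.3 and 0.5. This no-loss condition is also an assumption.
- **Cause of the shortfall.** It would be wrong to blame all of it on the repeated-measures contrast. The missing square and the 0.80 already leave a post-only test at about 77–79%, and at r of about 0.5 the group-by-time contrast is no worse than that.
- **Reach.** A reader might conclude that the SSI comparison is underpowered too. Under the stated rates it is not.

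**Conclusion.** The point holds in a limited form. The 80% stated for nurses is not derived for the planned pre/post controlled analysis, and the printed formula is itself defective. Under a flat control group, equal baselines of 44.8% and equal correlation in both arms, the planned contrast at 78:156 has about 58% to 86% power for r from 0.2 to 0.6 and passes 80% at about 0.53. With all 82:164 analysed, the threshold is about 0.50. Whether the trial lies above or below it cannot be settled from the document, which gives no correlation. The conclusion is therefore that 80% is not a reliable property of the nurse analysis, not that the analysis is shown to be underpowered. It does not extend to the SSI comparison in mothers.

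**What to change.** In *Sample estimation*:

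1. Correct the printed formula: square the braces and use 0.84 for Z-beta. Since the corrected formula no longer yields 78, present 82/164 as the planned numbers and report the power they give.
2. Replace the 80% statement for nurses with the power of the GEE group-by-time contrast at 82/164 over a stated range of correlations, for example 59%, 71%, 79% and 87% at r = 0.2, 0.4, 0.5 and 0.6, with the assumptions on baseline and control change written out. Bring the repeated 80% statement in *Analysis of SSI* into line.
3. Label the mothers' SSI power as that of a two-group post-intervention comparison.

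The Phase III pre-test of 50 nurse-midwives can inform the correlation only in part. It classifies knowledge as above or below the mean, whereas Phase 4 uses 75% of the maximum score, so its scores would have to be re-cut at 75%. All 50 are trained, so the control-arm correlation remains an assumption. An observed 0.5 would carry a 95% interval of roughly 0.26 to 0.68 (Fisher transformation: 0.549 ± 1.96/√47).

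No extra participants or data are needed for this restatement. The cost is a less favourable stated power for nurse knowledge.

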#### Ethical issues

Prior to the start of the study, ethical clearance and approval will be obtained from the Muhimbili University of Health and Allied Sciences (MUHAS) Institutional Board Review (IRB). Then, permission to conduct the study will be obtained from TAMISEMI, Regional Medical Office (RMO), District Medical Office (DMO) and lastly, from the medical officer and ward in charge, where the study participants will be obtained. The informed consent will be obtained and signed by all participants after the aim of the study has been explained to them, along with benefits and harm (if any). The confidentiality of the participants in the data will be highly maintained. To achieve this, confidential identification numbers will replace the names of post-CS mothers and will only be available to the PI and supervisors. Mothers who will have SSI and post-partum anaemia will be referred to be reviewed by a doctor for further treatment and follow-up.

Nurse midwives and post-CS mothers in the control group will be exposed to the guide after the study. This will be done to ensure equal benefits for both interventional and control groups.

## Discussion

The establishment of this guide will also help to cement the need for pre-discharge health education counselling for nurse midives to post-CS mothers and the entire community on home care practices. This will help Ministry of Health to incorporate the guide national wide, with the aim of improving home care after CS na reducing CS complications such as SSI. The limitations of the study include the risk of desirability bias, as participants may not feel comfortable giving honest feedback about their care. This will be prevented by ensuring post CS mothers that their responces will not be shared with their nurse mideives or caretakers hence they should feel free to share them with researcher. Another limitation is the the risk of SSI, which might be increased by other factors like multiple vaginal examinations during labour, time of rupture of membrane, duration of operation, existing medical condition of a woman like HIV/AIDs and diabetes, anaemia status, lack of antibiotics prophylaxis during the pre-and post-operative period and infection in the amniotic fluid. To mitigate this, adequate information regarding labour and operation procedure will be considered from the patient’s file and medical history is recorded from post-CS mothers, which will be used in the inclusion criteria of study participants and data analysis. have been adjusted by the statistical analysis in the statistical model.

The study findings will be published in reputable journals and presented at scientific conferences. The guide produced in this study will be shared with the Tanzania Ministry of Health, for possible adoption on the training of post-CS mothers in health facilities. The final dissertation report will be submitted to MUHAS and UDOM libraries.
